## Abstract

**Background:**

Latino men in the United States report low physical activity (PA) levels and related health conditions (eg, diabetes and obesity). Engaging in regular PA can reduce the risk of chronic diseases and yield many health benefits; however, there is a paucity of interventions developed exclusively for Latino men.

**Objective:**

To address the need for culturally relevant PA interventions, this study aims to develop and evaluate Hombres Saludables, a 6-month theory-based, tailored web- and text message-based PA intervention in Spanish for Latino men. This protocol paper describes the study design, intervention, and evaluation methods for Hombres Saludables.

**Methods:**

Latino men aged 18-65 years were randomized to either the individually tailored PA internet intervention arm or the nutrition and wellness internet control arm. The PA intervention included 2 check-in phone calls; automated SMS text messages; a pedometer; a 6-month gym membership; access to a private Facebook group; and an interactive website with PA tracking, goal setting, and individually tailored PA content. The primary outcomes were feasibility, acceptability, and efficacy (minutes per week of total moderate-to-vigorous PA assessed via the ActiGraph GT3X+ accelerometer worn at the waist and 7-day physical activity recall at baseline and 6 months). Secondary outcomes examined potential moderators (eg, demographics, acculturation, and environmental variables) and mediators (eg, self-efficacy and cognitive and behavioral processes of change) of treatment effects at 6 months post randomization.

**Results:**

This study was funded in September 2016. Initial institutional review board approval was received in February 2017, and focus groups and intervention development were conducted from April 2017 to January 2018. Recruitment for the clinical trial was carried out from February 2018 to July 2019. Baseline data collection was carried out from February 2018 to October 2019, with a total of 43 participants randomized. Follow-up data were collected through April 2020. Data cleaning and analysis are ongoing.

**Conclusions:**

We developed and tested protocols for a highly accessible, culturally and linguistically relevant, theory-driven PA intervention for Latino men. Hombres Saludables used an innovative, interactive, web- and text message–based intervention for improving PA among Latino men, an underserved population at risk of low PA and related chronic disease. If the intervention demonstrates feasibility, acceptability, and preliminary efficacy, we will refine and evaluate it in a larger randomized control trial.

**Trial Registration:**

Clinicaltrials.gov: NCT03196570; https://clinicaltrials.gov/ct2/show/NCT03196570

**International Registered Report Identifier (IRRID):**

DERR1-10.2196/23690

## Introduction

### Background

Engaging in regular physical activity (PA) exerts health benefits, including decreases in all-cause mortality, obesity, and risk for other chronic diseases, such as cardiovascular disease, type 2 diabetes, certain cancers, obesity, hypertension, osteoporosis, osteoarthritis, depression, and dementia [1]. Compared with White non-Latino men, more Latino men do not meet national PA guidelines (49.5% vs 38.9%) for leisure time PA [2,3]. Although several studies show that disparities in overall PA are not as pronounced in Mexican American men when measuring PA objectively, overall levels of PA are still too low in this population [4-7]. Latino men are disproportionately burdened by PA-related health conditions, such as obesity and overweight status (81.8% vs 75.3%) [8] and type 2 diabetes (12.5% vs 7.5%) [9]. This lack of PA signifies a substantial public health problem. Furthermore, there is heterogeneity across Latino subgroups. National data have revealed that Cubans and Dominicans had the lowest leisure time PA levels, whereas Mexican Americans were the most active [10]. Thus, Latino men from subgroups other than Mexican Americans may be at even higher risk for inactivity.

Although several studies have demonstrated the efficacy of culturally and linguistically appropriate, individually tailored PA interventions for Latina women [11-15], PA intervention studies with Latinos have excluded male participants or had limited numbers of men [16-18]. Most PA interventions with Latinos feature activities perceived by participants as more traditionally feminine (eg, dance classes) and targeted more female-specific barriers (eg, childcare duties) [19]. Multiple systematic reviews have found that no PA interventions have specifically targeted Latino men [16-18,20]. Since the last review published in 2019 [18], 2 small PA interventions (n=45-50) with mostly Mexican American men have been published. One study included an intensive in-person intervention, which has limited scalability [21], whereas the other involved individually tailored print materials and text messages sent to participants on a tapered schedule for 6 months [22].

This study addresses the scarcity of interventions designed to increase PA specifically for diverse Latino men and uses technology to improve reach and accessibility. Computer-based, expert system–driven, theory-based interventions use participant-supplied data to generate messages tailored to the individual needs of each participant [23]. They have shown great promise for providing effective, widely available, and low-cost health promotion programs [24,25]. This approach may appeal to Latino men as it addresses barriers identified in formative research, such as lack of time, family involvement, work responsibilities, and transportation [26-28], using a technology-based (internet and cell phone) tailored intervention. Technology-based approaches can help overcome PA barriers reported by Latinos in our formative research (eg, lack of time and transportation) and may be especially appropriate given the rapid rise in recent years in internet use among this population. In fact, as of 2019, a large majority of Latinos reported using the internet (86%) [29] and owning a cell phone (96%) [30]; smartphones accounted for 79% of cell phones [30]. Latinos are also more likely than non-Latino Whites to use their mobile devices (smartphones or tablets) to access health information [31], suggesting that technology-based PA interventions may be especially appealing to Latino men.

Recent meta-analyses (and a comprehensive review) have described the impact of web-based interventions on PA and have found small to moderate positive effect sizes [32-34]. For mobile device–based PA interventions, one meta-analysis found a moderate effect size (g=0.54) [35]. In addition, a systematic review of texting interventions found that strong evidence exists for integrating text messages into PA trials [36]. Thus, an individually tailored, multimedia web- and text-based intervention has the potential to broadly reach Latino men at a relatively low cost, which could help reduce low PA–related health disparities.

### Objectives

The purpose of this protocol paper is to describe the study design, intervention, and evaluation methods for Hombres Saludables, an internet- and text-based tailored Spanish language intervention designed for an ethnically diverse population of Latino men (ie, Caribbean and Central and South American origin) to increase total PA. This intervention was adapted from our culturally and linguistically appropriate, internet-based PA intervention for Latina women, Pasos Hacia la Salud [14], which successfully increased and maintained total PA levels in Latina women over 12 months [15,37].

## Methods

### Overall Design

Hombres Saludables is a 6-month randomized controlled trial (RCT) for Latino men comparing an individually tailored, internet- and text-based PA intervention with a control group that received an attention-matched intervention about nutrition and wellness. The primary aims of the study are to determine the feasibility, acceptability, and preliminary efficacy of the intervention, as well as the recruitment, implementation, and evaluation protocols. Secondary aims include examining potential moderators (eg, demographics, acculturation, and environmental variables such as the neighborhood and socioeconomic environments) and mediators (eg, self-efficacy and cognitive and behavioral processes of change) of treatment effects at 6 months post randomization. The targeted sample size for this pilot trial is 50 Latino men.

### Design Considerations

To inform the design of this study, we conducted 8 focus groups with 38 Latino men in Rhode Island. We asked their opinions on potential design elements of this study, including website functionality, use of text messages, email and social media, and content for both the intervention and control arms of the study. All focus groups were audio-recorded, and the recordings were transcribed, translated, and subjected to several stages of analytic coding using ethnographic methods by 2 graduate students. Transcripts were initially read as texts to isolate obvious themes and then subjected to open coding to identify additional themes and actions that are relevant for further analysis. Next, transcripts were subjected to focused coding using the subdomains identified in the earlier stages. Following coding, we worked with the coded data set and the texts to create a componential analysis that identified patterns and themes. Focus group findings were discussed with the research team and used to adapt and refine recruitment and intervention materials to be culturally appropriate for the diverse target audience. Focus group results will be discussed in another paper; however, briefly, participants expressed interest in the use of text messages rather than email to deliver information and reminders during the intervention. Focus group participants also recommended the use of a private Facebook group as a forum to post intervention content for study participants and allow them to comment and post among themselves. Focus group participants expressed strong interest in a gym membership, stating that it would help with barriers of cost and motivation to exercise.

### Participants and Eligibility

Inclusion criteria were as follows: (1) self-identification as Hispanic or Latino; (2) self-identification as male; (3) age between 18 and 65 years; (4) self-reported 60 min or less of total MVPA a week; (5) had an adequate literacy level to read study materials in Spanish, that is, scored more than 16 on the Spanish language version of the Short Test of Functional Health Literacy in Adults (S-TOFHLA) [38-40]; and (6) owned a cell phone with texting capabilities and had regular internet access via a smartphone, tablet, or computer. Eligible participants also had to agree to be assigned to either of the 2 treatment conditions.

Exclusion criteria were as follows: (1) history of myocardial infarction or angina, insulin-dependent diabetes, or hospitalization for diabetes in the past year; (2) stroke, osteoarthritis, osteoporosis, orthopedic problems, or exercise-induced asthma; (3) any other medical condition that would make MVPA unsafe; (4) hospitalization because of a psychiatric disorder in the past 3 years; (5) BMI >45; (6) planned surgery or hospitalization in the next 6 months; and (7) intake of medication that may impair PA tolerance or performance. Any questions about medical eligibility were sent to the study physician to determine eligibility. Participants who reported another family member already enrolled in another PA study being conducted concurrently by our research team were yoked during randomization to the same study arm to prevent the possibility of cross-treatment contamination.

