#### Visit 2 (PA Assessment and Randomization Session)

In-person participants returned for a second visit approximately 8 days after the first visit. They brought the accelerometer and the wear-time log form to the visit. Any participant with insufficient wear time (<3000 min over 4 days or <5 days of 600 min each) was asked to rewear the accelerometer, and the visit was rescheduled. Participants with sufficient wear time completed a 10-min treadmill walk to demonstrate moderate-intensity PA (3-4 miles per hour). Heart rate and rate of perceived exertion were documented throughout the treadmill walk by the study staff. The goal of the walk was to help improve the accuracy of participants’ self-report of their PA by providing a real-time demonstration of a 10-min bout of moderate-intensity PA with no breaks. The protocol for this demonstration was developed by [name] and has been used in earlier studies [11-13,64]. Participants then completed a 7-day PAR [62,63]. If participants reported more than 60 min of total MVPA in bouts lasting 10 min or more, they became ineligible.

Participants were then randomized to 1 of the 2 Spanish language internet and text message–based conditions: tailored PA intervention arm or nutrition and wellness control arm. Group assignment was determined using a permuted block randomization procedure with small randomly sized blocks. Randomization was stratified by the TTM stage of change [42,43] to ensure an equal distribution of treatment assigned across levels of motivational readiness for PA.

At the end of visit 2, the study staff helped participants in the tailored PA intervention arm to set up their personalized website account. The study staff also set up a bookmark to the page on the participant’s smartphone to aid easy access to the website and then provided thorough instructions on using all sections of the website. In the final phase of the visit, the study staff helped the participants set a personalized exercise goal and create a detailed PA plan for their first week. The staff members and the participants discussed potential barriers to completing this goal and how to overcome those barriers. The staff members walked the participants through these goal-setting steps and how to record their minutes of MVPA and goal on the website to ensure that the participants were able to complete these steps independently throughout the 6-month intervention.

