#### Power Analysis

Our sample size estimates were based on results from 2 of our completed studies with accelerometer data for Latina participants [12,15]. In addition, in a small pilot [19], the mean change from baseline to 6 months in MVPA from the subsample of male participants who were given accelerometers was 76.4 min per week (SD 113.5) for the intervention versus 15.0 min (SD 22.6) for the control. Although the effect size (*d*=0.75) was large, the subsample was small (N=9) and, thus, must be considered with caution. In our recently completed intervention with Latinas [15], the mean change in total MVPA was 42.5 min per week (SD 81.8) for the intervention versus 9.0 min (SD 45.7) for the control, yielding an effect size of *d*=0.51. With 25 participants randomized to each arm, we expected to have at least 43% power to detect differences in accelerometer-measured MVPA between conditions at 6 months, assuming an effect size of *d*=0.51 and 75% power if *d*=0.75, using a two-tailed significance α of .05. The web-based program for Latinas had a slightly higher effect size; therefore, this was a conservative estimate. Although we do not expect to achieve statistically significant group differences in this pilot study, we will determine the effect size achieved between groups and use these data to estimate the sample size needs for a future RCT.

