#### Planned Analyses

The primary aim of this study is to determine the feasibility, acceptability, and preliminary efficacy of the tailored PA intervention. We will consider the intervention feasible if at least 80% of the randomized participants are retained at the 6-month follow-up. The intervention will be considered acceptable if at least 80% of participants completing the 6-month follow-up respond favorably (*satisfied* or *very satisfied*) to the question *In general how satisfied were you with the intervention?* on the 6-month follow-up survey. We also asked more questions about intervention and study acceptability on the 6-month survey and the poststudy qualitative interviews described earlier. The main efficacy outcome was minutes per week of total MVPA, as measured by accelerometer data and PAR self-report, assessed at baseline and 6 months after baseline. The hypothesis is that participants in the PA intervention condition will have greater increases in minutes of total MVPA from baseline to post intervention (6 months) than participants in the control condition.

As a preliminary step, we will assess potential between-group differences in baseline characteristics (demographics and baseline PA level) using graphical methods and nonparametric and parametric tests as appropriate (eg, the Wilcoxon rank sum test for skewed data, *t* tests for normally distributed continuous data, and chi-square tests for categorical data). Any variables not balanced by randomization will be controlled for as covariates in subsequent analyses if they are correlated with the outcome (eg, minutes per week of MVPA) at a modest *P*<.10 level. We will estimate the preliminary efficacy of intervention compared with control using a generalized linear model in which we regress minutes per week of objectively measured MVPA at 6 months on the treatment assigned, baseline value of the outcome, and potential confounders (including those variables not balanced by randomization). To avoid the effects of outliers, we apply a normalizing transformation (if necessary) to the outcome before analysis. Should this transformation not adequately bring the data toward normality, we will model the median outcome (instead of the mean) using a quantile regression model.

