Modeling is performed using a likelihood or quasi-likelihood–based approach and, thus, makes use of all available data (intent-to-treat sample) to produce consistent estimates of the regression parameters. Our goal is to estimate effect sizes, rather than strict statistical hypothesis tests. A similar modeling strategy will be used to estimate effects on self-reported minutes per week of MVPA.

Potential moderators will be examined using a similar analytic approach to that described earlier. For example, the total PA at 6-month follow-up (as measured by the accelerometer) will be regressed simultaneously on each moderator (eg, neighborhood PA environment profiles), as determined by latent class analysis, treatment assignment, and the interaction between the 2. If the interaction term is nonzero, we will conclude that there is evidence for a potential moderator. Models will also control for potential confounders of the association, including baseline PA and any variables unbalanced between arms. Our interest is in estimating effect sizes for conditional effects rather than strict statistical hypothesis testing.

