### Study Limitations and Strengths

Although the strengths of this study are numerous, a few potential challenges exist. Recruitment and retention of Latinos in PA interventions are often challenging [106], and it is possible that there are unforeseen confounding factors that may impact the study results. However, the purpose of this pilot RCT is to determine the feasibility, acceptability, and preliminary efficacy of the intervention. Although contamination is often a concern when implementing interventions, we do not expect this to be a significant problem. If members of the same family participated, they were yoked together. In addition, the PA Facebook group membership was accessible only to participants in the PA intervention, and the web- and text message–based components were tailored to each participant. Despite these potential limitations, the Hombres Saludables study aims to increase PA among diverse Latino men by engaging them in a culturally appropriate, low-cost, and easily accessible internet and cell phone–based intervention. The intervention also provided economic incentives, including a gym membership, to overcome the cost barriers associated with PA. To our knowledge, no studies have included all the combined intervention components that are incorporated into the Hombres Saludables study. We expect that this study will demonstrate preliminary efficacy and lead us to implement a larger RCT in the future. This intervention has the potential to be scalable and to reach and engage a large number of diverse Latino men, a disparity group with respect to PA and related chronic diseases and mental health [1,2,8-10,18].

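### Men yoked to a relative's arm are not assigned by this trial's randomization, yet the efficacy analysis pools them with everyone else; this can bias the effect size

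*Protocol article*

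**What the plan says.** The article describes allocation in three places.

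- **Participants and Eligibility.** "Participants who reported another family member already enrolled in another PA study being conducted concurrently by our research team were yoked during randomization". The sentence goes on to say that they "were yoked during randomization to the same study arm to prevent the possibility of cross-treatment contamination".
- **Visit 2 (PA Assessment and Randomization Session).** "Group assignment was determined using a permuted block randomization procedure with small randomly sized blocks", and "Randomization was stratified by the TTM stage of change". No exception for yoked men appears here. Distance participants are said to follow the same procedure.
- **Study Limitations and Strengths.** "If members of the same family participated, they were yoked together". This is wider: it can be read as covering relatives who are both in this trial.

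On the analysis, Planned Analyses says "we regress minutes per week of objectively measured MVPA at 6 months on the treatment assigned, baseline value of the outcome", plus potential confounders. The modelling "makes use of all available data (intent-to-treat sample) to produce consistent estimates of the regression parameters". Neither statement sets yoked men apart.

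The article does not give the number of men yoked, the design of the concurrent study, or how that study's arms correspond to the arms here.

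**The concern.** A man's arm is randomized in this trial only if this trial's blocks and strata produce it. For a yoked man they do not: the arm follows from a relative who was enrolled earlier. Three routes from there to a biased comparison are plausible.

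1. **Enrolment that depends on the arm.** The relative's arm already exists, so the man, his household or the staff may be able to infer his. The arms differ in appeal. Design Considerations reports strong interest in a gym membership, and Study Incentives gives it at the start in the PA arm but only at 6 months in the control arm. Eligibility also turns on an interviewer-administered activity recall with a 60-minute limit, completed just before allocation.
2. **Uneven split.** Yoked men bypass the blocks and the stage-of-change strata, so nothing balances them between arms. If they differ in prognosis, an excess in one arm shifts the comparison.
3. **Household exposure.** Materials encourage exercising with family. If the concurrent study's PA arm is similar, a yoked PA man may live with a treated relative and a yoked control man may not. That is a different contrast from treating one man.

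What is at stake is the effect size. Power Analysis says the observed effect will be used to size a future RCT, and in a trial of 43 a few men carry weight.

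**Working it through.** **1. The plan's own figure.** The article states: "With 25 participants randomized to each arm, we expected to have at least 43% power to detect differences in accelerometer-measured MVPA between conditions" at d=0.51, and 75% at d=0.75, with two-sided alpha 0.05. The normal approximation is power = Φ(d·√(n/2) − 1.96) with n=25.
- d=0.51: 0.51 × 3.536 − 1.96 = −0.157, giving 43.8%.
- d=0.75: 0.75 × 3.536 − 1.96 = 0.692, giving 75.5%.
- The noncentral t gives 42.4% and 73.8%.

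The stated power reproduces. It treats all 25 men per arm as individually randomized and makes no allowance for yoking.

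**2. Bias from yoked men.** Let k_I and k_C be the numbers yoked in the intervention and control arms, n the men per arm, and δ_I and δ_C how far yoked men differ from the others in SD units after adjustment for baseline MVPA. Then

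bias = (k_I·δ_I − k_C·δ_C) / n.

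If δ is the same in both arms, this becomes (net excess) × δ / n. The article gives neither the number yoked nor δ, so I assume a net excess of 1 to 4 and δ of 0.25 to 1. Arm sizes are not given either; I take equal arms, n = 43/2 = 21.5.

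- N=43, smallest: 1 × 0.25 / 21.5 = 0.012 SD, 2% of d=0.51.
- N=43, middle: 2 × 0.5 / 21.5 = 0.047 SD, 9%.
- N=43, largest: 4 × 1 / 21.5 = 0.186 SD, 36%.
- N=50, range: 1 × 0.25 / 25 = 0.01 SD to 4 × 1 / 25 = 0.16 SD.
- Even split with the same δ: zero.

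The cancellation needs δ_I = δ_C. Selection on a known arm, or household exposure, can make them differ. With 2 yoked men in each arm, δ_I = 0.5 and δ_C = 0, the bias is again 2 × 0.5 / 21.5 = 0.047 SD.

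**3. Consequence for the next trial.** Suppose the true d is 0.51 and the pilot reports 0.61, an inflation of 0.10 that lies inside the range above. For 80% power, n per arm = 2 × (1.96 + 0.842)² / d².
- d=0.51: 15.70 / 0.2601 = 60.4, so 61 per arm.
- d=0.61: 15.70 / 0.3721 = 42.2, so 43 per arm.
- True power with 43 per arm: Φ(0.51 × √21.5 − 1.96) = Φ(0.405) = 66%.

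**4. Clustering.** This arises only if relatives are both in this data set or two men share one outside relative. With a fraction f of men in pairs and intraclass correlation ρ, the design effect is 1 + fρ. For f = 0.05 to 0.20 and ρ = 0.1 to 0.5 (assumed), it runs from 1.005 to 1.10. A nominal 0.05 test that ignores the pairs then has true alpha 2 × [1 − Φ(1.96/√DE)] = 0.051 to 0.062.

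**5. Cost of leaving yoked men out** (noncentral t, d=0.51).
- N=50: 42.4% with none left out; 40.9%, 39.4% and 38.0% with 2, 4 and 6 left out.
- N=43: 37.2% with none left out; 35.7%, 34.1% and 32.6% with 2, 4 and 6 left out.

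**The case against.** The strongest reply is that no harm is shown. The number yoked could be zero, and the limitations sentence is conditional. If the relative was randomized in the concurrent study, the inherited arm still comes from a random draw. A motivated family does not by itself create a difference between arms, because yoked men could enter either one. Yoking is an openly stated safeguard against contamination, and the pilot aims to estimate effect sizes rather than to test strictly. All of this stands, and it is why the point is worded as a risk.

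Four stronger readings are tempting but not supported:

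- **That the comparison is biased.** This needs one of the three routes above to have operated, and the article does not show that any did.
- **That staff or family knew the arm before enrolment.** The article places yoking at randomization, after consent, baseline survey, accelerometer wear and recall, and requires men to accept either condition. It does not say when family status was asked or who looked up the relative's arm. Prior knowledge is a reasonable inference and no more.
- **That the analysis assumes independence and so understates its intervals.** No such assumption is stated. A likelihood or quasi-likelihood approach could handle clusters, and the full analysis plan is not shown. Under the eligibility rule the relative is in another study, so one yoked man adds no correlation here.
- **That the bias could reach half the planning effect.** That takes 6 of 43 men yoked, all in one arm and each 1 SD different: 6 × 1 / 21.5 = 0.28 SD. Nothing in the article supports that combination.

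The objection does not remove the core. The article itself states an assignment rule outside its randomization and a pooled comparison by assigned treatment. That is more than silence on a detail left to an analysis plan.

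**Conclusion.** The point holds as a risk to the effect-size estimate. Yoked men were not assigned by this trial's stratified permuted blocks, their allocation may have been predictable, and the described efficacy analysis does not distinguish them. Under the assumed inputs, the bias from an uneven split is about 0.01 to 0.19 SD at N=43, with either sign, and zero if they split evenly. An even split does not remove bias from arm-dependent enrolment or from the relative's own treatment. Clustering is minor: true alpha at most about 0.062 under the assumed range, and only if relatives are both in the trial or men share one relative. Everything scales with the unreported number yoked; if it is zero or one, the matter is close to closed.

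**What to change.** - Flag yoked men in the data set and report their number by arm, saying whether the relative was in the concurrent study or in this trial.
- Give the efficacy estimate in independently randomized men beside the all-participants estimate, at least as a sensitivity analysis fixed before results by arm are seen. Which of the two is primary is open to debate. Having an enrolled relative precedes allocation, so leaving these men out does not disturb the randomized comparison among the rest. Where relatives are both in this trial, keep the member randomized first.
- Use family-clustered standard errors in the all-participants model if relatives are both in the data set.
- Base the future RCT's sample size on an effect size shown to be robust to leaving out yoked men.
- Keep yoked men in the retention and acceptability counts.
- Reconcile Participants and Eligibility, Visit 2, and Study Limitations and Strengths, so that one rule says who is yoked, to whom, and how this fits with the blocks and strata.

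The cost is one flag and one more model. The restricted estimate loses a few men: about 1.5 to 4.5 points of power at d=0.51 if 2 to 6 are left out of the planned 50. The article reports that data cleaning and analysis are still under way, so the change remains possible.
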